#### Prediction of Anxiety Symptomatology

2.9.2

For exploratory prediction analysis, we will compute an *Anxiety Factor Score*, yielding a single, streamlined, and reliable index of anxiety‐related psychopathology, based on Pittig et al. (2023), but using follow‐up‐based standardization. Each psychometric measure will be z‐standardized using the mean and standard deviation of the full sample at follow‐up and then averaged across anxiety‐related measures (i.e., BAI, PROMIS Anxiety, ASI‐3, PAS, SPAI, and PSWQ). Importantly, this composite reflects relative anxiety severity at follow‐up rather than intraindividual change over time.

To account for baseline differences in symptom levels, baseline anxiety will be included as a covariate in all longitudinal prediction models, thereby allowing the examination of predictors of follow‐up anxiety above and beyond initial symptom levels. Baseline anxiety will be operationalized as a composite score of anxiety symptomatology derived from the measures available at baseline, following the same general procedure as described above.

Next, linear mixed models expand the model of anxiety prediction and fear generalization with polygenic risk scores derived from publicly available Anxiety GWAS (Strom et al. 2024), cortisol awakening response (area under the curve of cortisol), early trauma and life events to explore each variable's contribution to anxiety. As described above, variability between time points will be included by modelling age as a quantitative variable and allowing for corresponding interactions with measurement timepoints. To further model this, we will also account for time‐warping in these analyses along the lines of the fdasrvf package in R (https://cran.r‐project.org/package=fdasrvf).

Moreover, random forest methods will integrate complex variables (e.g., GWAS and DNAm), combining multiple decision trees to obtain stable, accurate predictions via cross‐validation. Each tree votes, and the class with most votes determines the final classification. As predictors we will include fear generalization indices, psychometrics, life events, endocrine and molecular measures. Random forests resist overfitting, particularly under cross‐validation and with good predictive power. Besides, they handle missing data effectively, preserving predictive power.

For both the random forest and linear mixed models, we will use repeated nested cross‐validation to get a reliable estimate of generalization error expected in an unseen sample (see e.g. and following the ideas of Rost et al. 2022). In addition, we will perform permutation analysis encapsulating the complete prediction model building to investigate and confirm that the model building process as outlined per se will not lead to overfitting, meaning that the distribution of the performance metrics do indeed follow expectations under the null.

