### Recruitment

2.2

In this study, all Würzburg adults from two prior Z02 cohorts who completed the fear learning paradigm, as well as children and adolescents who participated in both earlier assessments and consented to recontact, are invited. This yields two timepoints for adults (T1 > T2) and three for youths (T1, T2 > T3; see Figure 1). Earlier assessments included extensive psychometric evaluations of anxiety symptoms, a fear conditioning and generalization paradigm, and genetic phenotyping.

Re‐recruitment is expected at ≥ 40% for adults and ≥ 50% for adolescents. Exclusion criteria include acute psychosis, suicidality, pregnancy, and illicit drug use (verified by urine toxicology). Unlike initial enrollments (Table 1), participants with psychopathologic traits are intentionally included to track longitudinal development.

**TABLE 1 mpr70094-tbl-0001:** Overview and eligibility criteria of the initial and follow up sample.

	A‐T1/1 and A‐T1/2	C‐T1 and C‐T2	Follow‐up
Inclusion criteria	Age between 18 and 50 years Caucasian background Right‐handedness Fluency in German	Age between — 8 and 12 years (C‐T1) or — 12 and 16 years (C‐T2) Caucasian background Right‐handedness Fluency in German	Participants of adult cohort A‐T1/1 and A‐T1/2 that performed the paradigm Participants of the child and adolescent cohort C‐T1 and C‐T2 that took part in both assessments
Exclusion criteria	Major clinical disorders Pregnancy Severe medical conditions Ongoing medication intake Use of illegal drugs as assessed by urine toxicology More than 14 glasses alcohol per week More than 20 cigarettes per day More than 4 cups caffeine per day	Severe somatic conditions Intake of psychoactive medication Low intelligence (IQ < 85)	Pregnancy Use of illegal drugs as assessed by urine toxicology

Participants are first contacted in writing (email or letter), followed by a telephone call to provide more details and confirm eligibility. Oral informed consent is obtained, and interested participants are invited to complete an additional CAR measurement. For those unable to visit Würzburg, online options are available for clinical interviews and psychometric assessments.

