### Current Procedure

2.3

All participants provide written informed consent. Prior to the experimental procedure, in a subgroup of participants samples for CAR analysis are collected following recommendations in Adam and Kumari (2009). Furthermore, all participants undergo urine testing to screen for substance use and pregnancy, followed by a diagnostic interview. Saliva samples for cortisol analysis are taken immediately before and after the fear acquisition and generalization paradigm, the study's core assessment, and blood samples are collected afterward. Participants then complete a comprehensive psychometric evaluation (see Figure 2 for an overview of the procedure). Remuneration is €50 for in‐person participation and €20 for online participation.

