#### Blood Cell Analysis

2.8.1

Blood samples are collected after the experimental paradigm to analyze blood cell composition and routine indices. The total blood volume collected is 18.1 mL, divided as follows: 9 mL EDTA for (epi)genetics and blood cell counts, 7.5 mL serum for metabolomics and hormone analyses, and 1.6 mL EDTA specifically for a differential blood count. Serum is centrifuged 20 min after collection at 2500g for 15 min at 4°C. Samples are stored at −80°C for later analysis. All participants had previously been genotyped at the genome‐wide association study (GWAS) level using high‐throughput genotyping arrays (1st wave PsychChip and 2nd wave GSA 3.0).

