#### HPA‐System

2.8.2

On the endocrine level, cortisol is measured from four saliva samples collected at home in the morning after awakening, using a provided test kit and instructions. Ideally, sampling occurs on the study day or a typical working day close to it: the first sample at awakening, followed by three more at 15‐min intervals over 45 min. Participants are asked to avoid food, drink, or physical activity, and are encouraged to remain in bed engaging only in low‐arousal activities such as reading. After collection, participants store the samples in a freezer until bringing them to the study site. If needed, the study team arranges sample pickup within the Würzburg area (for recommendations see Stalder et al. 2016, 2022). Additionally, two saliva cortisol samples are collected pre‐ and post‐fear generalization to assess task‐related stress responses.

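### If the optional cortisol awakening response (CAR) is fitted jointly with polygenic risk, trauma and life events, those estimates rest only on participants who gave CAR samples

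*Protocol article*

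**What the plan says.** Section 2.2 (Recruitment) describes CAR as an extra: "interested participants are invited to complete an additional CAR measurement". Section 2.3 (Current Procedure) agrees: "in a subgroup of participants samples for CAR analysis are collected". Neither section gives the size of this subgroup.

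Section 2.8.2 (HPA-System) adds the practical demands: four morning samples taken at home, kept in a freezer and brought to the site. If needed, "the study team arranges sample pickup within the Würzburg area". Section 2.2 also says that for people who cannot travel, "online options are available for clinical interviews and psychometric assessments".

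Section 2.9.2 (Prediction of Anxiety Symptomatology) expands the model of anxiety and fear generalization with PRS and "cortisol awakening response (area under the curve of cortisol), early trauma and life events", with the aim of seeing what each one adds. Baseline anxiety is a covariate in all longitudinal prediction models.

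The other added terms are not tied to the subgroup. Section 2.8.1 says of genotype: "All participants had previously been genotyped at the" genome-wide level. Table 2 places a childhood trauma screener and a life-event list in the follow-up battery.

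On missing data, section 2.9.2 says of random forests: "Besides, they handle missing data effectively, preserving predictive power". Section 2.9 allows analyses to be adjusted for missing data and names no method. Nothing is said about missing covariates in the mixed models.

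**The concern.** A likelihood-based mixed model can use people with missing outcomes, but it cannot use a row in which a covariate is missing. CAR is named in the same list as PRS, trauma and life events and is not set apart as a sub-analysis. Fitted jointly, a person without CAR drops out of every coefficient in the expanded model, and not only out of the CAR coefficient. No CAR value from an earlier wave can fill the gap, because Table 4 shows HPA measures at follow-up only.

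Part of the loss may be built into the design. An online participant can supply T1 generalization, baseline anxiety, genotype, trauma, life events and the follow-up anxiety score. That person has no site visit to which saliva could be brought, and pickup is local. The plan makes an effort to keep such people and may then lose them from the expanded model because of one optional covariate. At stake is the precision of the PRS, trauma, life-event and adjusted generalization estimates in one of the three main research questions. Cross-validation run within the CAR subgroup would describe prediction error for people like its members, not for the whole cohort.

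**Working it through.** The article gives no sample size for the CAR subgroup or for the expanded model, so there is no figure to reproduce.

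**Inputs**
- Follow-up sample in the Discussion: 226 + 357 = 583.
- Alternative base, from the minimum re-recruitment rates in section 2.2 and the counts in Figure 1: 0.5 × 337 + 0.4 × (526 + 262) = 168.5 + 315.2 = 483.7, about 484.
- CAR uptake f: not given. Assumed at 70%, 50% and 30%.

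**Formulas**
- Participants left after row deletion: n = f × N.
- Standard-error ratio: 1/√f, assuming similar residual variance and covariate spread in the subgroup.
- Power for a correlation r, two-sided 5% (assumed): Φ(atanh(r) × √(n − 3) − 1.96).
- Correlation detectable with 80% power: tanh((1.960 + 0.842)/√(n − 3)).

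**Results**

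| Uptake | n of 583 | n of 484 | SE ratio | Power, r = 0.15 (base 583) | r at 80% power (base 583) |
|---|---|---|---|---|---|
| 100% | 583 | 484 | 1.00 | 95% | 0.116 |
| 70% | 408 | 339 | 1.20 | 86% | 0.138 |
| 50% | 292 | 242 | 1.41 | 73% | 0.163 |
| 30% | 175 | 145 | 1.83 | 51% | 0.210 |

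For example, at 70%: atanh(0.15) = 0.151; 0.151 × √405 = 3.04; 3.04 − 1.96 = 1.08; Φ(1.08) = 0.86.

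**Check of the mechanism.** A mixed model was fitted to one simulated data set of 583 people with CAR missing at random in about half. With CAR and incomplete rows dropped, 282 people remained and the PRS standard error was 0.063. Without CAR all 583 remained and it was 0.044. The ratio, 0.063/0.044 = 1.43, agrees with √(583/282) = 1.44.

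**Check for bias.** Ordinary regression, 1,500 simulated data sets of 583, about half with CAR. The coefficients are assumed: PRS 0.15, trauma 0.20, life events 0.20.

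| What CAR participation depends on | PRS | Trauma | Life events |
|---|---|---|---|
| Nothing | 0.150 | 0.200 | 0.199 |
| Trauma (a modelled covariate) | 0.150 | 0.198 | 0.200 |
| Follow-up anxiety, logit slope 0.5 | 0.143 | 0.189 | 0.187 |
| Follow-up anxiety, logit slope 1 | 0.127 | 0.167 | 0.164 |

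Loss of precision follows from row deletion alone. Bias needs participation that depends on follow-up anxiety given the covariates.

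**The case against.** The strongest reply is that row deletion is not written anywhere. Section 2.9.2 speaks of models in the plural that explore what each variable contributes. That could mean adding terms one at a time, and a full analysis plan could specify staged fitting or imputation of CAR. This stands as far as it goes: the confinement is conditional on joint fitting with the default handling. It does not remove the point, because the article itself lists a subgroup covariate beside full-sample ones without separating them. The remark on random forests does not extend to mixed models, and the general allowance in section 2.9 names no remedy.

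The analysis is labelled exploratory, which lowers the weight. The correlations of CAR with fear generalization in section 2.9.3 need only CAR participants and are untouched.

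A reader might also infer more than the documents support:
- *That the whole prediction aim is confined to CAR participants.* Section 2.9.2 expands an existing model of anxiety and fear generalization, so a model without CAR comes first and keeps its full sample.
- *That gain in fit from the basic to the expanded model is confounded with a change of sample.* No such comparison is planned in the text.
- *That the random forest needs the same split.* Cortisol around the task and serum for hormones are collected outside the CAR add-on, so endocrine data are not confined to the subgroup.

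**Conclusion.** The point holds in conditional form. If PRS, CAR, trauma and life events are fitted together and incomplete rows are dropped, the expanded model's PRS, trauma, life-event and adjusted generalization estimates describe CAR participants only. The cost is precision: standard errors about 20%, 41% or 83% larger at 70%, 50% or 30% uptake. These percentages are the same on a base of 583 or 484. The uptake values are assumptions, so the actual loss cannot be fixed from the article.

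A reader might take CAR participants' self-selection as proof of biased estimates. The documents do not show this. They give no information on how participation relates to follow-up anxiety, baseline anxiety is already adjusted for, and selection at random or on a modelled covariate left the simulated slopes essentially unchanged. This is a worthwhile, low-cost improvement to an exploratory analysis and does not undermine the study's main questions.

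**What to change.** In section 2.9.2:
1. Fit the expanded model with fear generalization, baseline anxiety, PRS, early trauma and life events in all participants who have these data.
2. Add CAR as a last step within the CAR subgroup, and compare it with the same model without CAR refitted in that subgroup.
3. Report the number with CAR, and compare those with and without it on baseline anxiety, age, cohort and T1 generalization.

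The random forest can stay as described.

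The cost is a few sentences and one extra model, the one without CAR, fitted in the full sample and again in the subgroup. No new data are needed. The downside is that CAR's contribution is reported for the subgroup only, which is all that the sampling scheme supports.

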**Conclusion:**

Our findings will clarify the long‐term stability of fear learning paradigms and evaluate their value as markers of anxiety risk. In addition, a random forest model will explore multiple risk factors and their interaction in anxiety symptomatology. This may improve understanding of anxiety disorders and support early detection and prevention.

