### Psychometry

2.6

To analyze the trajectory of anxiety symptomatology and its interaction with environmental factors, we employ an assessment battery based on measures from previous assessments (see Table 2 for details). We deliberately modified the battery to prioritize instruments that best capture psychopathology at follow‐up for predictive purposes, rather than adhering strictly to continuity with prior assessments.

**TABLE 2 mpr70094-tbl-0002:** Overview of psychometrics across assessments.

Construct	Instrument	A‐T1/1	A‐T1/2	C‐T1	C‐T2	Follow‐up
Sociodemographic, health behavior	General questionnaire	X	X	X (P)	X (P)	X
Psychopathology	MINI	X	X			
	Kinder‐DIPS			X (C + P)	X (C + P)	
	Mini‐DIPS					X
	CGI					X
Intelligence	CFT‐20 R			X (C)	X (C)	
General anxiety symptomatology	STAI‐T	X	X			
	STAI‐C			X (C)	X (C)	
	BAI	X	X			X
	DSM‐5 dimensional anxiety scales		X			
	PROMIS anxiety					X
Anxiety sensitivity	ASI	X	X			
	CASI			X (C)	X (C)	
	ASI‐3	X	X			X
Panic/agoraphobia	ACQ	X	X			
	PAS					X
Social anxiety	LSAS	X	X			
	SPAI	X	X			X
	SPAIK			X (C)	X (C)	
Generalized anxiety	PSWQ	X	X			X
Phobias	FAS	X	X			
	PHOKI			X (C)	X (C)	
	ASA‐27		X			
	TAI			X (C + P)	X (C + P)	
General psychopathology	PROMIS‐29 profile (modified)					X
	BSI‐18					X
	YSR (screening)			X (C)	X (C)	
	CBCL (screening)			X (P)	X (P)	
Depression	ADS‐K	X	X			
	BDI‐II		X			X
	DIKJ			X (C)	X (C)	
Emotion regulation	CERQ short	X	X			
Affectivity	PANAS trait	X	X			
Intolerance of uncertainty	UGTS					X
Rejection sensitivity	RSQ‐9					X
Social desirability	SDS‐CM	X	X			
Temperament	TEMPS		X			
Behavioral approach	BIS/BAS	X	X			
Coping	Brief‐COPE		X			
	GSE	X	X			
Stress	TICS		X			X
	KFB		X			
	SVF‐78		X			X
	SVF‐K			X (C)	X (C)	
Social support	BSSS		X			X
	SS‐A		X			
Resilience	KIDSCREEN‐27			X (C + P)	X (C + P)	
	SDQ			X (C + P)	X (C + P)	
Parental behavior	ESF			X (P)	X (P)	
	PBQ‐AC‐M			X (P)	X (P)	
Parents' psychopathology	BAI			X (P)	X (P)	
	BDI‐II			X (P)	X (P)	
	SCL‐90‐R			X (P)	X (P)	
Life events	Life calendar	X	X (mod.)			
	LTE	X	X (mod.)			
	ZLEL			X (C)	X (C)	
	Munichs event list					X (mod.)
Childhood traumata	CTQ	X	X			
	CTS					X

*Note:* (C) = Self‐report by children and adolescents; (P) = Parent report.

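### If one random forest covers adults and youths, its cross-validated accuracy can come from cohort membership alone, and neither the missing-data statement nor the planned permutation check guards against that

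*Protocol article*

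**What the plan says.** The abstract's conclusion announces that "a random forest model will explore multiple risk factors and their interaction in anxiety symptomatology". Section 2.9.2 of the protocol article lists the inputs: "As predictors we will include fear generalization indices, psychometrics, life events, endocrine and molecular measures". It does not say from which wave the psychometrics and life events come. On incomplete data it says: "Besides, they handle missing data effectively, preserving predictive power".

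The outcome is a composite of six follow-up anxiety scales, each "z‐standardized using the mean and standard deviation of the full sample at follow‐up". Baseline anxiety enters the longitudinal prediction models as a composite "derived from the measures available at baseline, following the same general procedure as described above".

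Two safeguards against overfitting are named. One is repeated nested cross-validation. The other is described as follows: "we will perform permutation analysis encapsulating the complete prediction model building". The section states no stratification by cohort, no permutation within cohort and no cohort-specific reporting of performance.

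**The concern.** The adult and youth batteries at the earlier waves hardly overlap. For an earlier-wave questionnaire, whether the value is present then tells the algorithm whether the person belongs to the adult or the youth cohort. Scales given only in A-T1/2 also separate the two adult cohorts. The outcome is standardized over everyone at follow-up, so any youth-adult mean difference stays in it. A forest fitted to all participants could exploit that difference.

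Aim 2 concerns the prediction of later anxiety from fear learning and other risk factors. Accuracy that only separates 16- to 22-year-olds from adults does not answer it. It could nevertheless be reported as multi-factor risk prediction, with high importance given to questionnaires that merely mark the cohort.

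**Working it through.** The plan gives no figure to reproduce here, so the check has four steps.

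**1. Count of Table 2 (section 2.6).** Parents' own scales are counted with the youth cohort.

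| | Rows |
|---|---|
| All instrument rows | 59 |
| Used at an earlier wave | 49 |
| Adults only | 29 |
| of these, A-T1/2 only | 10 |
| Youths only | 19 |
| Both | 1 |

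The one shared row is the general questionnaire, a parent report in youths: "General questionnaire X X X (P) X (P) X". By cohort, A-T1/1 has 19 + 1 = 20 instruments, A-T1/2 has 29 + 1 = 30, and youths have 19 + 1 = 20. So 48/49 = 98% belong to adults alone or youths alone. Life events, a named predictor, split in the same way: the Life calendar and LTE in adults, the ZLEL in youths.

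**2. What cohort membership alone can explain.** Let p be the share of youths and d the youth-adult difference in the outcome, in within-cohort SDs. Then R² = d²p(1−p) / [1 + d²p(1−p)].

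The Discussion gives 226 youths and 357 adults, so p = 226/583 = 0.388 and p(1−p) = 0.237. At the planned minimum rates, 50% of 337 is about 168 youths and 40% of 788 is about 315 adults, so p = 0.348 and p(1−p) = 0.227. The documents do not give d, so it is an assumption.

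| d (assumed) | R², 226/357 | R², 168/315 |
|---|---|---|
| 0 | 0% | 0% |
| 0.3 | 2.1% | 2.0% |
| 0.5 | 5.6% | 5.4% |
| 0.7 | 10.4% | 10.0% |

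For example, at d = 0.5 with 226/357: 0.25 × 0.237 = 0.0593, and 0.0593/1.0593 = 5.6%, a correlation of 0.24.

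**3. Does a forest pick this up?** A small simulation used 226 youths and 357 adults with pure-noise predictors (10 adult-only, 8 youth-only, 6 shared). Missing values were coded out of range. It used five-fold cross-validation and six replicates per d. The mean cross-validated correlations were:

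| d | Pooled | Within youths | Within adults |
|---|---|---|---|
| 0 | −0.02 | −0.01 | −0.04 |
| 0.3 | 0.08 | −0.04 | −0.06 |
| 0.5 | 0.23 | −0.02 | 0.00 |

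A second simulation (N = 484, 40 noise predictors in two cohort-exclusive blocks, median imputation, ten folds) gave about 0.15 at d = 0.5, against 0.04 with no cohort difference. The size depends on how missing values are treated; the direction does not.

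**4. Do the stated safeguards catch it?** Unstratified folds contain both cohorts, so a cohort label learned in training also predicts in the held-out fold. Permuting the outcome over all participants destroys the cohort-outcome link together with every other association. The null distribution then centres near zero, and a pure cohort effect exceeds it. Permuting within cohort keeps the cohort difference in the null, so only prediction beyond cohort can exceed it.

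**The case against.** The strongest reply is that two premises are not written down.

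- **Pooling.** The abstract's singular wording and the full-sample standardization suggest one forest, but the second describes how the outcome is scaled, not who enters the model. Where the article pools explicitly, in the age-trajectory models of section 2.9.1, it says so. A reader might infer that a pooled forest is planned; the documents support this only as the likelier reading.
- **Earlier-wave scales as predictors.** The wave is not given. The baseline composite exists for both cohorts, and everyone is assigned one follow-up battery that includes a life-event list and a trauma screener. A reader might also compute a large share of data missing by design by treating all 49 instruments as separate columns. Nothing in the article says that they enter in that form, and several have adult and child counterparts that could be harmonised.

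Both objections stand, and the point is therefore conditional.

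It is also fair that the missing-data sentence may be meant for ordinary gaps, such as awakening cortisol in a subgroup only, online-only participants or excluded skin-conductance non-responders. As worded, however, it has no such limit. Missingness is also not the only route: age, if it is a predictor, separates most of the cohorts with complete data. Removing the sentence would therefore not be enough, which is why evaluation within cohort matters more.

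The article describes the forest as classifying by majority vote. R² and r then only illustrate the size, although the same mechanism acts on classification accuracy. Finally, separate forests or centring the outcome within cohort are modelling choices, not corrections, since centring would also remove a real age-related difference in risk.

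**Conclusion.** The point holds in conditional form. The general missing-data claim cannot apply to instruments that a whole cohort never received, and that describes 48 of the 49 earlier-wave instruments when adults and youths are compared. If one forest is fitted to both cohorts with such instruments, age or other cohort-related predictors, and if mean follow-up anxiety differs between cohorts, pooled performance can exceed chance with no within-cohort prediction. At an assumed difference of 0.3 to 0.7 SD the cohort-only R² is about 2% to 10%; at zero difference there is no artefact.

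The documents do not show that the forest will be invalid, because they settle neither the pooling, nor the wave of the predictors, nor the size of the cohort difference. What can be said is that the safeguards as described would not detect the artefact, and that a nearly free change would. The prediction work is labelled exploratory, so the weight is modest.

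**What to change.** In section 2.9.2:

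1. Qualify the missing-data sentence so that it does not cover instruments never given to a cohort.
2. State whether the forest is pooled. If it is, use only predictors available or harmonised across cohorts: the common follow-up battery (apart from the six scales that form the outcome), the baseline anxiety composite, fear indices from a wave that every cohort has, and molecular measures.
3. Stratify the folds by cohort (A-T1/1, A-T1/2, youths) and permute the outcome within cohort.
4. Report cross-validated performance within each cohort next to the pooled figure.

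Forests fitted separately with each cohort's own battery are an optional sensitivity analysis.

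Items 3 and 4 need no new data and cost no sample size. Item 2 gives up cohort-specific scales in the pooled model. The optional separate forests have a smaller n: about 315 adults and 168 youths at the planned minimum rates, or 357 and 226 by the Discussion's figures. The other costs are a little more analysis work and possibly a less favourable accuracy figure.
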